## Abstract

**Background:**

Cesarean section (CS) requires perioperative antibiotic prophylaxis (PAP) for the prevention of surgical site infections. However, systemic antibiotics during the peripartum period may induce compositional perturbations of the maternal gut microbiome, a system already characterized by reduced resilience. Data on maternal gut microbiome dynamics after CS with PAP are scarce, largely due to logistical and feasibility barriers that limit the participation of pregnant women and new mothers in conventional clinical studies.

**Objective:**

This protocol primarily aims to evaluate the feasibility of a fully decentralized, remote study design for longitudinal gut microbiome research in the peripartum period. Secondary exploratory objectives include the comparative analyses of microbiome composition between CS with PAP and vaginal delivery (VD) without antibiotic exposure to inform future adequately powered studies.

**Methods:**

The MAMA (Microbiome Changes Due to Antibiotic Prophylaxis in Mothers at Birth) study is a prospective, 2-arm observational cohort study conducted entirely off-site. Women in the third trimester of pregnancy were recruited at 2 German level-1 perinatal centers and affiliated outpatient facilities. Participants underwent either CS with PAP (single dose cefuroxime 1.5 g intravenously) or VD without antibiotics. Stool samples were self-collected at home and returned by mail at 3 predefined time points: late pregnancy (T0), 2 to 3 days post partum (T1), and 90±10 days post partum (T2). Primary outcomes are feasibility indicators, including recruitment rate, sample and questionnaire return rates at each time point, adherence to sampling windows, and participant retention across follow-up. Secondary outcomes are exploratory microbiome measures based on 16S rRNA gene sequencing (V3-V4), including alpha diversity indices, beta diversity metrics, and relative taxonomic abundances. Microbiome analyses are explicitly compositional and hypothesis-generating. Group comparisons and longitudinal within-individual changes will be assessed using nonparametric diversity metrics and multivariate distance–based methods. No confirmatory hypothesis testing is planned.

**Results:**

Recruitment occurred between May 2022 and October 2023, with 37 women enrolled (25 CSs and 12 VDs). Follow-up was completed with receipt of the final stool sample in March 2024. DNA extraction and sequencing were completed in a single batch in October 2024. Bioinformatic processing and statistical analyses were initiated in June 2025 and are ongoing as of December 2025. Results from the exploratory microbiome analyses are expected to be published in 2026.

**Conclusions:**

This protocol demonstrates the feasibility of conducting fully decentralized, longitudinal microbiome research in a peripartum population without requiring on-site visits. By integrating study procedures into maternal realities, the remote design reduces participation barriers and addresses a clinically relevant research gap that has remained largely unexamined despite routine use of PAP. While microbiome-related outcomes are exploratory, the methodological framework established here provides a scalable model for future maternal and postpartum research, supporting ethically grounded, participant-centered study designs and evidence-informed care strategies.

## Introduction

### Background

Cesarean section (CS) accounts for a substantial and steadily increasing proportion of births worldwide (21% in 2021), representing one of the most common surgical interventions performed in otherwise healthy women [1]. Nevertheless, it carries the third-highest incidence of surgical site infections among all surgical interventions [2]. To reduce postoperative infectious morbidity, perioperative antibiotic prophylaxis (PAP) is universally recommended and constitutes a central component of obstetric surgical safety, as endorsed by major gynecological societies and supported by World Health Organization (WHO) guidelines [3-5]. Recommended prophylactic regimens typically involve a single preincisional intravenous dose of a first- or second-generation cephalosporin, although other antibiotic classes may be used based on local epidemiology and formulary structures. In Germany, cefuroxime is the only antibiotic explicitly approved for cesarean prophylaxis, providing reliable coverage of pathogens commonly associated with postcesarean infections [6]. This universal application of PAP represents an essential protective measure but simultaneously introduces a systemic antibiotic exposure during a physiologically dynamic period for postpartum women.

Short-term systemic antibiotic exposure is known to modulate gastrointestinal microbial communities. Even a single perioperative dose can induce compositional and diversity changes in gut microbial communities, affecting metabolic function and the relative abundance of commensal and opportunistic organisms [7,8]. During pregnancy, endocrine and immunometabolic adaptations reshape the gut microbiome toward lower diversity and increased inflammatory tone, resulting in reduced ecological stability. These pregnancy-associated shifts inherently diminish microbial resilience, potentially heightening vulnerability to additional perturbations such as perioperative antibiotics, postoperative dysmotility, or transient inflammatory responses following cesarean delivery [9,10].

Antibiotics administered intravenously during CS reach high systemic levels and can exert direct antimicrobial activity within the intestinal lumen. Pharmacologically active luminal concentrations have been demonstrated for parenterally administered cephalosporins via biliary excretion [11-13]. In addition, postoperative physiological changes, including transient gastrointestinal dysmotility, reduced oral intake, shifts in hormonal and immune activation, analgesic use, and surgical inflammation, further influence microbial composition [14,15]. Clinically, systemic antibiotic exposure is associated with postantibiotic diarrhea, which may involve overgrowth of opportunistic taxa such as *Clostridioides difficile*, illustrating that short, prophylactic antibiotic regimens can perturb microbial homeostasis even in otherwise healthy individuals [16,17]. Together, these mechanisms support the biological plausibility that PAP could induce measurable, short-term compositional changes in the maternal gut microbiome.

Despite this plausibility, empirical evidence specific to postpartum women is remarkably scarce. The maternal gut microbiome during the peripartum and immediate postpartum period has received far less research attention than neonatal colonization or vertical microbial transmission. Alterations in maternal microbial communities could influence metabolic recovery, immune reconstitution, gastrointestinal symptoms, inflammation, wound healing, and overall well-being. However, the postpartum period is underrepresented in microbiome research because traditional, visit-based study designs impose substantial logistical burdens on new mothers. A recent review underscored this gap, highlighting the near absence of high-quality studies evaluating maternal gut microbiome dynamics following CS and PAP [18].

### Rationale for the Study Design

A central methodological consideration is the need for an appropriate comparator. PAP cannot be randomized for ethical reasons as withholding it would contradict the standard of care. Assessing only pre-post changes within CS patients would confound potential antibiotic effects with postoperative physiological responses. A vaginal birth comparison group therefore provides a meaningful counterfactual, capturing physiological postpartum microbial trajectories in the absence of surgical intervention and perioperative antibiotics. However, existing literature is an insufficient substitute for such a comparator, as microbiome datasets vary widely in sequencing region (eg, V1-V2 vs V3-V4), primer selection, read depth, and bioinformatic processing (operational taxonomic unit–based clustering vs amplicon sequence variant [ASV] inference) [19,20]. These methodological discrepancies substantially limit cross-study comparability and hinder valid inference from aggregated external controls. A contemporaneous comparator group is therefore essential for exploratory evaluation of whether postpartum microbial trajectories differ following CS with PAP.

Postpartum research also faces substantial feasibility challenges. New mothers often have limited mobility, competing care demands, and little capacity for additional clinical visits [21]. These barriers disproportionately exclude women from participating in research and limit the representativeness of available data. To address these constraints, we developed a fully remote, participant-centered protocol using at-home stool collection and postal submission. Remote sampling approaches have demonstrated strong feasibility in other areas of microbiome research [22,23], but they have not yet been systematically applied to postpartum maternal populations. Such designs reduce participation burden, enhance accessibility across geographic and socioeconomic contexts, and provide a pragmatic framework for capturing real-world postpartum microbial patterns.

Given the achieved sample size and group imbalance, this study is primarily framed as a feasibility investigation assessing recruitment, adherence, and the performance of remote stool sampling in the early postpartum period. Secondary exploratory analyses aim to characterize maternal gut microbiome composition and diversity following CS with PAP compared with vaginal birth, to evaluate short-term microbial trajectories, and to identify hypothesis-generating taxonomic patterns. These analyses are not powered for confirmatory inference but will inform the design of future, adequately powered studies.

Although PAP is a universal component of CS, its potential impact on the maternal gut microbiome remains insufficiently understood. This protocol addresses this gap by implementing a remote, participant-centered study design that enables feasible, scalable, and ethically grounded investigation of postpartum microbiome dynamics.

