### Objectives

The primary objective of the MAMA (Microbiome Changes Due to Antibiotic Prophylaxis in Mothers at Birth) study is to assess the feasibility of a fully remote, nonsite-bound study design for longitudinal gut microbiome research in a peripartum population, including recruitment, sample return, and follow-up completion.

Secondary objectives are to explore compositional changes in the maternal gut microbiome associated with PAP using cefuroxime during CS, compared with vaginal delivery (VD), across the peripartum period.

In this context, the study aims to establish a scalable methodological framework for future remote microbiome studies in maternal health and other vulnerable populations.

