**Figure 1. F1:**
[figure not shown]
Study design of the MAMA (Microbiome Changes Due to Antibiotic Prophylaxis in Mothers at Birth) trial: fully remote workflow and sample collection schedule. CS: cesarean section; PAP: perioperative antibiotic prophylaxis; VD: vaginal delivery.

The study was originally conceptualized as a hypothesis-testing cohort design aimed at characterizing maternal gut microbiome trajectories in relation to delivery mode and PAP exposure. However, real-world recruitment constraints in this peripartum population resulted in a smaller and unevenly distributed sample size. In view of these conditions, the present protocol primarily serves as a feasibility investigation of a fully decentralized study framework for maternal microbiome research. Accordingly, subsequent microbiome analyses are defined as exploratory and hypothesis-generating rather than confirmatory.

A contemporaneous comparator group was required to interpret microbial patterns observed after CS. Randomization or withholding of the standard of care was ethically impermissible, and pre-post analyses within CS alone would have conflated antibiotic-associated effects with surgical and physiological consequences of operative delivery. VD therefore represented the most appropriate counterfactual, reflecting postpartum microbial trajectories in the absence of PAP and operative stress. External control datasets were not considered suitable due to widely recognized methodological heterogeneity across microbiome studies (eg, primer regions, sequencing workflows, and bioinformatic pipelines), which limits cross-study comparability.

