### Eligibility and Recruitment

Participants were eligible for inclusion if they were aged at least 18 years, in the third trimester of pregnancy, and planned to deliver either by elective CS or VD without medical indication for peripartum antibiotics. Sufficient German language skills were required to complete the informed consent process and written study documentation. Exclusion criteria comprised participation in another clinical study, chronic inflammatory bowel disease (eg, Crohn disease or ulcerative colitis), hematologic or oncologic disease, chronic renal or hepatic disease, and chronic viral infections such as HIV, hepatitis B virus, or hepatitis C virus. Additional exclusions included systemic use of immunosuppressants, virostatics, cytostatics, proton pump inhibitors, or systemic antimicrobial agents (antibiotics or antifungals) within the past 3 months. Women with a foreseeable need for surgery or antimicrobial treatment other than cefuroxime within the study period (90 days postpartum) were also excluded.

Participants were recruited between May 2022 and October 2023 at 2 German level 1 perinatal centers and affiliated outpatient facilities. Eligible women were identified by attending obstetricians and midwives during routine clinical care. To support recruitment beyond the hospital setting and to address recruiting bias, awareness of the study was raised through posters in clinic waiting areas, printed flyers distributed during antenatal visits, and social media announcements via the official channels of the participating institutions. In addition to reaching a broader population, the social media strategy was specifically intended to include women with low-risk pregnancies who received all prenatal care in the outpatient sector and would otherwise have had limited contact with hospital-based recruitment. This approach aimed to reduce recruitment bias toward high-risk pregnancies, such as those with gestational diabetes, multiple gestation, or prior cesarean delivery. Pregnant women and new mothers represent a population with specific logistical and time-related needs, which informed the choice of a decentralized recruitment and study design.

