## Results

The recruitment and sample collection phase of the study has been completed. Between May 2022 and October 2023, a total of 37 participants were enrolled, including 25 women in the CS group and 12 in the VD group. Recruitment concluded below the originally planned sample size, reflecting real-world constraints in this peripartum population. Follow-up was completed with receipt of the final stool sample in March 2024. An overview of baseline characteristics of participants who returned at least one stool sample is presented in Table 1. DNA extraction and 16S rRNA gene sequencing were completed in a single batch in October 2024. All samples passed quality control and were retained for downstream analyses. An overview of included and excluded samples by group and time point is provided in Figure 2. Bioinformatic processing and statistical analyses were initiated in June 2025 and were ongoing as of December 2025.

**Table 1. T1:** Baseline characteristics of participants who submitted at least 1 sample (N=31)^a^.

Characteristic		Total (N=31)	CS^b^ with PAP^c^ (n=20)		VD^d^ without PAP (n=11)	
Continuous variables						
Age (y), median (IQR)		37 (33-39)	37 (33-39)		36 (33-38)	
Categorical variables, n (**%**)						
Delivery mode						
CS		20 (65)	20 (100)		—^e^	
VD		11 (35)	—		11 (100)	
Multiple births						
Yes		2 (6)	2 (10)		0 (0)	
No		29 (94)	18 (90)		11 (100)	
Parity						
0		12 (39)	9 (45)		3 (27)	
1		13 (42)	5 (25)		8 (73)	
2		5 (16)	5 (25)		0 (0)	
3		0 (0)	0 (0)		0 (0)	
4		0 (0)	0 (0)		0 (0)	
5		1 (3)	1 (5)		0 (0)	
>1		19 (61)	11 (55)		8 (73)	

a Only participants in the CS group received PAP; no antibiotics were administered in the VD group.

b CS: cesarean section.

c PAP: perioperative antibiotic prophylaxis.

d VD: vaginal delivery.

e Not applicable.

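### The vaginal-delivery group cannot separate antibiotic prophylaxis from cesarean surgery, so the secondary objective should name the combined exposure

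*Protocol article*

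**What the plan says.** The argument for a comparator appears twice in the protocol article.

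- **Rationale for the Study Design** first names the problem: "Assessing only pre-post changes within CS patients would confound potential antibiotic effects with postoperative physiological responses". It then offers the remedy: "A vaginal birth comparison group therefore provides a meaningful counterfactual, capturing physiological postpartum microbial trajectories in the absence of surgical intervention and perioperative antibiotics".
- **Study Design and Setting** (text after Figure 1) repeats both steps. The problem is that "pre-post analyses within CS alone would have conflated antibiotic-associated effects with surgical and physiological consequences of operative delivery". The conclusion is that "VD therefore represented the most appropriate counterfactual, reflecting postpartum microbial trajectories in the absence of PAP and operative stress".

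The **Objectives** section words the secondary aim as to "explore compositional changes in the maternal gut microbiome associated with PAP using cefuroxime during CS, compared with vaginal delivery (VD".

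Three places fix how PAP and delivery mode relate:

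- Rationale for the Study Design: "PAP cannot be randomized for ethical reasons as withholding it would contradict the standard of care".
- Eligibility and Recruitment: women "planned to deliver either by elective CS or VD without medical indication for peripartum antibiotics".
- Footnote a to Table 1: "Only participants in the CS group received PAP; no antibiotics were administered in the VD group".

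The last paragraph of **Principal Findings** disclaims a causal aim, plans stratification and adjustment for confounding, and links the residual confounding it expects to the modest, imbalanced sample. **Limitations** covers power, unequal groups, relative abundance without absolute quantification, and incomplete follow-up. Neither says that PAP and surgery cannot be told apart.

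**The concern.** The word that links problem and remedy, in both sections, is 'therefore'. The stated problem is that antibiotic and surgical effects are mixed within CS. A comparator helps with that only if it differs from CS in one of the two factors. The VD group differs in both.

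The article itself gives reasons to expect surgery to act on the outcome. Its Background lists transient dysmotility, reduced oral intake, analgesics and surgical inflammation as influences on microbial composition. A difference between the groups at 2 to 3 days postpartum (T1) could thus arise from the operation, the cefuroxime dose, or both.

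What is at stake is interpretation. A reader of Objectives would expect the CS-VD contrast to say something about PAP as such. The article also aims to inform later studies, and under Comparison With Prior Work it points them to larger and more balanced cohorts. A larger study with the same two arms would have the same limit.

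**Working it through.** The article gives no figure to reproduce here, because the question is one of identifiability. The check uses its own group sizes.

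**Step 1. Cross-table of exposure by delivery mode (Table 1 column headings and footnote a).**

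| | PAP | No antibiotics |
|---|---|---|
| CS | 20 | 0 |
| VD | 0 | 11 |

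Both off-diagonal cells are empty, and the design keeps them empty: PAP is not withheld in CS, and women planning VD with an indication for peripartum antibiotics are not eligible. Women who took other antimicrobials are treated as protocol deviations, so they do not fill these cells in the per-protocol set.

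**Step 2. What each comparison contains.** Write the change from late pregnancy to a postpartum time point, on an additive scale, as the sum of

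- *t*: common peripartum course,
- *s*: effect of the operation and its consequences,
- *a*: effect of PAP.

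Then:

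- Pre-post change in CS = *t* + *s* + *a*
- Pre-post change in VD = *t*
- Difference CS − VD = *s* + *a*

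The VD group removes *t*. The sum *s* + *a*, which is the mixture the article objects to in a pre-post CS design, is left as it was.

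**Step 3. Rank of the cross-sectional model.** With columns [1, CS, PAP] and PAP = CS for every woman:

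- 25 CS and 12 VD (enrolled): correlation of CS and PAP = 1.0; rank 2 of 3.
- 20 CS and 11 VD (Table 1): correlation = 1.0; rank 2 of 3.

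**Step 4. Rank of the longitudinal model.** The columns are intercept, T1, T2, CS, CS×T1, CS×T2, PAP×T1 and PAP×T2, eight in all. The rank is 6 of 8 for both sets of group sizes. The two lost dimensions are PAP×T1 and PAP×T2, which are identical to CS×T1 and CS×T2.

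**Step 5. Sample size and covariates.** The PAP column equals the CS column whatever the number of rows, so recruiting more women to the same two arms leaves the rank deficiency in place. Adding covariates such as parity, medication, diet or allergies adds columns but does not make PAP differ from CS. Stratifying does not help either, since no stratum can contain women with and without PAP within one delivery mode.

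**The case against.** The strongest reply has four parts.

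1. **The article does not expressly claim that VD separates PAP from surgery.** Both key sentences say openly that VD lacks the two factors, and Rationale for the Study Design ends by asking about trajectories after CS with PAP. This stands as far as it goes. But the separation problem is the only reason given just before 'therefore', so the inference still does not follow.

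2. **The joint exposure is already the usual wording.** The Abstract's objective, the Rationale and the hypotheses under Outcomes compare CS with PAP against VD. This stands, and it limits the correction: Objectives is the statement of aim that needs changing, while the hypotheses can stay. Even there the wording is associational and places PAP within CS.

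3. **VD is a sound comparator for the combined exposure and removes the shared peripartum trend.** This stands. A reader might infer that the VD group is worthless or that the word counterfactual must go. The documents do not support that; what fails is the particular reason given for it.

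4. **The analyses are exploratory, causal aims are disclaimed, residual confounding is expected, and group comparability is to be addressed in the results paper.** This lowers the consequence but does not remove the gap. 'Residual' implies partial control, and for PAP against surgery there is none. The article ties the remainder to sample size and imbalance, which are not the cause.

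A reader might also infer that analgesia and diet are as inseparable from PAP as the operation is. The documents do not show this. Medication and diet are recorded and meant for exploration or adjustment, and the cross-table concerns delivery mode only.

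**Conclusion.** The point holds as one of interpretation. The CS-VD contrast estimates the combined effect of cesarean and PAP (*s* + *a*). It carries no information on PAP apart from cesarean, at any sample size of this design and with any covariate set. The secondary objective, read as being about PAP using cefuroxime, goes beyond that, and the stated limitations leave this out.

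It would be too strong to say that the secondary objective cannot be answered at all: only the PAP-specific reading is out of reach, and the descriptive contrast of the two bundles can be estimated. Nor can it be said that the results will be misattributed, since the results paper is not among the documents. The primary feasibility outcomes do not depend on the contrast and are unaffected.

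The conclusion rests on Table 1 and its footnote: every CS woman contributing a sample received PAP and no VD woman received antibiotics. The additive form in Step 2 serves illustration only. If surgery and PAP interact, the interaction also falls within the combined contrast.

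**What to change.** Four changes of wording:

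1. **Objectives.** Reword the secondary aim as the comparison of CS with PAP (combined exposure) against VD without antibiotic exposure, in line with the Abstract and Outcomes.
2. **Rationale for the Study Design and Study Design and Setting.** Replace the inference with the statement that VD controls for the common peripartum course and serves as comparator for the combined exposure only.
3. **Principal Findings (confounding paragraph) and Limitations.** Add that PAP and operative effects coincide completely and cannot be separated by stratification, adjustment or a larger sample of the same design.
4. **Results paper.** Do not attribute differences to cefuroxime or PAP alone.

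The cost is a few sentences and a narrower claim. No sample, test or estimate changes. As the article reports analyses still ongoing in December 2025 and plans the results paper for 2026, the wording can be settled before that paper is written.
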